## Abstract

**Background:**

Psychological interventions which adopt an explicitly interpersonal approach are a recent development in the treatment of distressing voices. AVATAR therapy is one such approach which creates a direct dialogue between a voice-hearer and a computerised representation of their persecutory voice (the avatar) through which the person may be supported to gain a sense of greater power and control. The main objective of the trial is to test the clinical efficacy of this therapy to reduce the frequency and severity of auditory verbal hallucinations (AVH). Secondary objectives of the study are to explore explanatory mechanisms of action and potential moderators, to carry out a qualitative evaluation of participants’ experience and to conduct an economic evaluation.

**Methods/Design:**

The AVATAR randomised clinical trial will independently randomise 142 participants to receive either 7 sessions of AVATAR therapy or supportive counselling (SC). The study population will be individuals with schizophrenia spectrum and other psychotic disorders who report hearing persistent distressing voices, for more than 12 months, which are unresponsive or only partially responsive to antipsychotic medication. The main hypotheses are that, compared to SC, AVATAR therapy will reduce the frequency and severity of AVH and will also reduce the reported omnipotence and malevolence of these voices. Assessments will occur at 0 weeks (baseline), 12 weeks (post-intervention) and 24 weeks (follow-up), and will be carried out by blinded assessors. Both interventions will be delivered in a community-based mental health centre. Therapy competence and adherence will be monitored in both groups. Statistical analysis will follow the intention-to-treat principle and data will be analysed using a mixed (random) effects model at each post treatment time point separately. A formal mediation and moderator analysis using contemporary causal inference methods will be conducted as a secondary analysis. The trial is funded by the Welcome Trust (WT).

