### Assessments and follow-up

There are 3 assessment points: at baseline before randomisation, at 12 and 24 weeks. All measures apart from weekly in-session measures will be carried out by trained research staff. Participants will complete a number of self-completed and interview-based measures to assess the impact of interventions on outcomes and to explore potential mediators and moderators of therapy. All the assessment sessions will be audio-recorded to ensure the accuracy of data collection. The participants will be reimbursed £20 plus any travel expenses for each assessment session in recognition of their time and other out-of-pocket expenses.

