### Measures

The primary outcome measure of the study is the total score on the auditory hallucinations subscale of the Psychotic Symptoms Rating Scale (PSYRATS-AH [28]) at the 12-week follow-up. It is an interviewer-assessed measure of the frequency and duration of auditory hallucinations over an average week. The PSYRATS is specifically designed for use with people suffering from psychosis, with inter-rater reliability ranging from 0.79 to 1.00 and high validity when compared with similar psychiatric scales [28]. It has been extensively used in research with these populations and has been shown to be acceptable to service users.

Secondary outcome measures will include the Revised version of the Beliefs about Voices Questionnaire (BAVQ-R, [29]: a self-report measure which focuses on the patient’s beliefs about the voices, and indexes how likely the voices are to affect behaviour. In addition to the total score, changes in two subscales will be analysed: omnipotence and malevolence.

Other standardised measures will be used to assess changes in voice experience and appraisals: the Voice Acceptance and Action Scale: VAAS [30] and Voice Power Differential Scale: VPDS [10]. We will assess changes in delusions using the Psychotic Symptoms Rating Scale: PSYRATS-D [28] and other psychotic symptoms using the Scale for Assessment of Positive and Negative Symptoms: SAPS and SANS [31]. Other standardised questionnaires will assess anxiety and depression (Depression Anxiety and Stress Scale: DASS-21 [32]; (Calgary Depression Scale [33]); self-esteem [34]; quality of life (Short Assessment of Quality of Life, MANSA [35]); and illicit drug use [36].

In order to assess progress during the therapy, the PSYRATS-AH [28] and the VPDS [10] will be completed by the therapist and the participant at each therapy session. Additionally, an adapted version of the Sense of Presence Questionnaire [37], the State Social Paranoia Scale [38] in relation to the avatar along with analogical scales will be used to assess the participant’s interaction with the avatar and the match obtained during the creation of the image/voice. Burns Empathy Scale [39] will be completed in sessions 2, 4 and 6. All the questionnaires in the study are being delivered in paper-and-pencil format.

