### Analysis

#### Statistical analysis

Analysis will be conducted in Stata version 13 (StataCorp, College Station, TX, USA) [40]. Descriptive statistics within each randomised group will be presented for baseline values. These will include counts and percentages for binary and categorical variables and means and standard deviations, or medians with lower and upper quartiles, for continuous variables, along with minimum and maximum values and counts of missing values. There will be no tests of statistical significance or confidence intervals for differences between randomised groups on any baseline variable.

The primary hypothesis for change in the severity of auditory hallucinations as measured by the total PSYRATS-AH score will be analysed using a mixed (random) effects model allowing for the baseline measurement of PSYRATS-AH and treatment assignment as fixed effects, at 12 weeks. This takes account of missing outcomes assuming a missing at random mechanism which allows missingness to depend on baseline severity of AH and treatment assignment. Therapist effects will be modelled by including a random effect for each therapist in the two therapy conditions. The use of a mixed (random) effect models will allow for estimation of the intra-cluster correlation coefficient, a measure of the proportion of variance in outcome because of therapist effects, which can be used in future applications; no estimate of this is currently available. Secondary outcome measures will be analysed using the same modelling approach. This includes analysis of the primary outcome and secondary outcomes at 24 weeks.

A secondary mediation analysis will investigate putative mediational factors (including beliefs about voices, self-esteem, anxiety/levels of distress) using modern causal inference methods. This involves using parametric regression models to test for mediation of the AVATAR therapy on AH through the putative mediators. Analyses will adjust for baseline measures of the mediator, outcomes, and possible measured confounders. We will include repeated measurement of mediators and outcomes to account for classical measurement error and baseline confounding, and instrumental variable methods (baseline covariate by randomisation interactions as potential instruments) to investigate the sensitivity of the estimates to these problems and that of unmeasured confounding [41].

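### Modelling each visit separately leaves the 12-week score out of the 24-week analysis; one model of both visits would make the maintenance result more robust at little cost

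*Protocol article*

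**What the plan says.** The Abstract (Methods/Design) says that "data will be analysed using a mixed (random) effects model at each post treatment time point separately". The Statistical analysis section describes the primary model as "allowing for the baseline measurement of PSYRATS-AH and treatment assignment as fixed effects, at 12 weeks", and adds: "Therapist effects will be modelled by including a random effect for each therapist in the two therapy conditions". It states that missing outcomes are handled under a "missing at random mechanism which allows missingness to depend on baseline severity of AH and treatment assignment". Secondary outcomes use the same approach, and "This includes analysis of the primary outcome and secondary outcomes at 24 weeks".

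On timing, the Assessments and follow-up section says: "There are 3 assessment points: at baseline before randomisation, at 12 and 24 weeks". The primary outcome (Measures) is the auditory hallucinations total on the "Psychotic Symptoms Rating Scale (PSYRATS-AH [28]) at the 12-week follow-up". The Research objectives and hypotheses section also lists, as a trial hypothesis, that the benefit of AVATAR therapy persists at 24 weeks. The Sample size section allows for 20% loss to follow-up.

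No term linking a participant's two follow-up scores is described.

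**The concern.** A mixed model fitted to one visit has one outcome per participant, and its only random effect is for therapist. For the treatment effect it behaves as a baseline-adjusted comparison of those who attended that visit, with allowance for therapist clustering. A participant without that visit's score adds nothing to that visit's estimate, even if the other follow-up score is on file.

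Missingness may then depend on baseline severity and arm, as the article says, but not on how the participant was doing at 12 weeks. Response at 12 weeks is an obvious candidate for influencing who returns at 24 weeks. If that influence differs between arms, those who attend at 24 weeks are a differently selected group in each arm, and the comparison that tests maintenance is biased. The score needed to correct this is already collected. Some precision is lost as well.

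**Working it through.** **The plan's own figure.** For d = 0.6, two-sided 0.05 and 90% power, n per arm = 2(1.960 + 1.282)²/0.6² = 58.4, so 59. Then 59 × 1.2 = 70.8, which gives the stated 71. With 20% loss, 71 × 0.8 = 56.8 complete per arm. Power with 57 is 89.3% (normal) or 88.8% (t test), close to the stated 90%. The implied SD is 5/0.8 = 6.25 points, so d = 0.6 is 3.75 points.

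**Where bias would come from.** Write the 24-week score as linear in arm, baseline and 12-week score, with coefficient g on the 12-week score. If attendance at 24 weeks depends only on those three, then

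bias of the separate 24-week model = g × (adjusted arm difference at 12 weeks among 24-week attenders − the same difference among everyone).

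The bias is zero when dropout leaves the 12-week arm difference unchanged, and grows with the distortion of that difference. A joint likelihood model replaces the attenders' 12-week difference with everyone's.

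**Inputs.** From the article: 142 participants, 1:1, d = 0.6, 20% loss. Assumed, because the article gives no values: correlation r of baseline with each follow-up score 0.3-0.5; correlation s between 12 and 24 weeks 0.6-0.8; log-odds of missing week 24 rising by 0.5 or 1 per SD of 12-week score. Therapist effects were left out, and everyone was assumed seen at 12 weeks.

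**Simulated bias of the separate 24-week model** (1,000,000 participants per run, true effect −0.60 SD; negative values exaggerate the AVATAR benefit):

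| Dependence of dropout on 12-week score | r 0.5, s 0.7 | r 0.3, s 0.6 | r 0.5, s 0.8 |
|---|---|---|---|
| None | 0.003 | 0.001 | 0.003 |
| Same in both arms, log-odds 0.5 | 0.013 | 0.011 | 0.011 |
| Same in both arms, log-odds 1 | 0.032 | 0.033 | 0.037 |
| AVATAR arm only, log-odds 0.5 | −0.045 | −0.051 | −0.054 |
| AVATAR arm only, log-odds 1 | −0.077 | −0.086 | −0.097 |
| Opposite, +1 AVATAR and −1 SC | −0.159 | −0.177 | −0.196 |

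The joint estimate was within 0.004 SD of the truth in every large run. With no true effect, equal dependence gave no bias. Reversing who drops out reverses the sign of the arm-specific rows.

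In points (× 6.25), equal dependence gives 0.011-0.037 SD = 0.07-0.23. One-arm dependence at d = 0.6 gives 0.045-0.097 SD = 0.28-0.61. Opposite dependence gives 0.159-0.196 SD = 0.99-1.23.

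As an illustration of the formula with r 0.5 and s 0.7: g = (0.7 − 0.25)/(1 − 0.25) = 0.6. A bias of −0.077 thus means that dropout shifted the adjusted 12-week arm difference by −0.077/0.6 = −0.13 SD.

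The small bias under equal dependence comes from unequal loss. At log-odds 1, 24% of SC and 16% of AVATAR participants were missing. When loss was held at 20% in each arm, the mean estimates were −0.599 and −0.604.

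**At trial size** (142 participants, 4,000 replicates, no true effect, r 0.5, s 0.7-0.8), the separate 24-week model had type I error of 5.0-5.2% with unrelated dropout, 8.3% with one-arm dependence at log-odds 1, and 17.5-20.9% with opposite dependence. The standard error was about 0.16 SD.

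**Precision.** With unrelated dropout, the ratio of joint to separate variance at 24 weeks is 1 − m × p², where m = 0.20 and p is the partial correlation of the two follow-up scores given baseline, (s − r²)/(1 − r²).
- r 0.5, s 0.7: p = 0.60, ratio 1 − 0.20 × 0.36 = 0.928 (simulated 0.929 and 0.913).
- r 0.5, s 0.8: p = 0.733, ratio 1 − 0.20 × 0.538 = 0.892 (simulated 0.904 and 0.898).

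The simulated saving is therefore roughly 7-10%. At 12 weeks, a separate simulation with 12% missing there and assumed correlations 0.5, 0.45 and 0.75 gave 4-5% more variance for the separate model. That gain comes only from people who miss week 12 but attend week 24.

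**Second check.** With the same three correlations and 20% missing at 24 weeks, the separate model gave −0.60 (unrelated dropout), −0.59 to −0.56 (equal), −0.65 to −0.71 (one arm) and −0.79 (opposite), against about −0.60 for the joint model throughout. The one-arm upper end, 0.11 SD, is slightly beyond the table.

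**The case against.** The Abstract and the Statistical analysis section agree with each other, and the missing-data assumption is stated openly. Under that assumption the separate models are valid. All of this stands, so the point cannot be called a contradiction or an error.

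A reader might infer that participants who miss one visit are discarded from the trial. They are not: someone lost after week 12 stays in the primary analysis. A reader might also infer that the primary result is biased. Dropout after week 12 cannot do that.

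A third tempting inference is that any dropout related to 12-week response biases the 24-week effect materially. The table shows otherwise: material bias needs a mechanism that differs by arm. One adverse run, with 24% missing at 24 weeks and only poorly responding AVATAR participants leaving, gave −0.72 SD against −0.60. That excess of 0.12 SD is 20% of the effect, but it rests on loss above the planned 20%, a one-sided mechanism and assumed correlations. The article does not predict arm-specific dropout. It gives some reason to consider it: SC participants are offered AVATAR therapy after the trial, a reason to stay that the other arm lacks, and five pilot participants did not complete therapy.

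Two further objections carry weight. A therapist effect shared across visits would add an assumption that the separate models do not need, and the simulations did not test therapist effects. An analysis plan that is not shown may add sensitivity analyses or predictors of missingness. Neither removes the gain at 24 weeks, because the separate-visit method is a choice the article itself states.

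**Conclusion.** The point holds as a cheap improvement in robustness for the 24-week result. At the planned 20% loss, the bias of the separate 24-week model ranges from nil (unrelated dropout), through about 0.01-0.04 SD towards the null (equal dependence) and 0.04-0.10 SD (one arm), to 0.16-0.20 SD (opposite). Against a standard error near 0.16 SD, the first two are minor; the third is roughly a quarter to three-fifths of a standard error, and the last is at least a full one. The direction depends on who leaves.

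These sizes rest on assumed correlations and dropout strengths, approximately normal scores and no therapist effect. The joint model removes bias from dropout that depends on observed scores. It does not protect against dropout that depends on the unseen 24-week score itself.

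**What to change.** Estimate the 12- and 24-week effects from one likelihood model of both follow-up scores. Fixed effects: arm, visit, arm × visit, baseline and baseline × visit. Use an unstructured within-participant covariance and a therapist random effect allowed to differ by visit where this can be estimated. Read each visit's contrast from that model, and use the same form for secondary outcomes measured at both visits. If the sponsor prefers to leave the 12-week primary model alone, apply the joint model at least to the 24-week contrasts. Keep the separate-visit models as a sensitivity analysis.

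Change the sentence in the Abstract and the model description in the Statistical analysis section to match, and restate the missing-data assumption so that missingness may also depend on the observed score at the other visit.

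Cost: wording and a few lines of code, with no new data and no change to the time-specific effects being estimated. The downside is a somewhat more complex model that may not converge if there are few therapists. The simplification to be used in that case, for example one therapist effect common to both visits, should be fixed in advance.

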**Discussion:**

AVATAR therapy showed promising effects in a pilot study, but the efficacy of the approach needs to be examined in a larger randomised clinical trial before wider dissemination and implementation in mental health services.

**Trial registration:**

Current Controlled Trials ISRCTN: 65314790, registration date: 27 March 2013.

## Background

Previous studies have shown that around 70 % of people with schizophrenia report auditory hallucinations [1]. Voice hearing or auditory verbal hallucination (AVH) is the most commonly reported form of auditory hallucinations [2, 3] and is typically defined as hearing a voice or other sound in the absence of an external stimulus [4]. These AVHs frequently provoke high levels of distress and interference in the daily lives of those who experience them and, therefore, have become a major target of psychological therapies for psychosis [5].

**Fig. 1 Fig1:**
[figure not shown]
Study flowchart

**Fig. 2 Fig2:**
[figure not shown]
Examples of avatars

Drawing on seminal early work from Chadwick and Birchwood, cognitive models of voice- hearing propose that beliefs about voices (specifically regarding identity, power, intention and control) are key to understanding distress and maladaptive responding [6, 7]. In their model, Morrison and colleagues specifically propose that auditory hallucinations occur when a person misattributes an internal experience (e.g. intrusive thought) to an external source [8]. It is argued that subsequent maladaptive appraisal processes are maintained by safety behaviours (including selective attention), faulty self-knowledge (including metacognition), social knowledge, mood and physiology [9]. Birchwood and colleagues [10, 11] developed their model by applying social rank theory [12, 13] to voice-hearing and found that individuals who experienced powerlessness and inferiority in social relationships were more likely to report similar experiences during the voice interaction [10, 14]. It is argued that early powerlessness and perceived inferiority in social relationships establish social schemata that drive subsequent appraisals of voices leading, in turn, to significant levels of distress and depression [11]. Recent reviews have provided support for the proposal that social schema may mediate the appraisal-distress relationship with the implication that therapies could benefit from targeting social and interpersonal variables [2, 14].

These theoretical developments have informed a specific cognitive therapy for command hallucinations [15, 16]. A randomised controlled trial of this approach [15] has recently reported a reduction in the rate of compliance compared with the treatment as usual group (odds ratio 0·45) along with an associated reduction in the specific treatment target (the power difference between the perceived threat of the voice and the hearer’s ability to mitigate this threat). Other approaches have also adopted an explicitly relational approach, targeting key aspects of the voice relationship including appraisals of relative power and assertiveness [17, 18].

More recently, AVATAR therapy has been developed as a relational approach by [name] [19, 20]. This builds on the previous theoretical and clinical developments within the context of a novel therapeutic milieu. The main goal of this therapy is to facilitate a dialogue between the patient and a computerised representation of their persecutory voice in which the voice hearer is assisted to gain control over the distressing voice. The approach uses computer technology developed by the Speech, Hearing and Phonetics Department at University College London which enables each participant to create a visual representation of the entity (human or non-human) that they believe is talking to them. Additional software is used to transform the voice of the therapist to match closely the pitch and tone of the voice the patient reports hearing, the two processes finally being combined to produce a computer simulation (a virtual agent or ‘avatar’) through which the therapist can interact with the participant. The therapist promotes a dialogue between the participant and the avatar in which the avatar progressively comes under the participant’s control. The sessions are audio- recorded and provided to the participant on an MP3 player for continued use at home [19].

### Pilot study

In an initial pilot study, comparing the therapy with a waiting list control group, a maximum of 7 sessions lasting 30 minutes resulted in highly significant reductions in the participants’ hallucinations and associated distress, as well as a reduction in scores on the omnipotence and malevolence subscales in the Revised version of the Beliefs about Voices Questionnaire (BAVQ-R) [19].

Researchers in the pilot study asked the participants how close a match there was between the image on the monitor or the voice they had selected and what they believed their persecutor looked and sounded like. Ratings of the match were not reported or explored as possible treatment moderators but two participants said the avatar was not a good representation of their hallucination [20]. In terms of feasibility, of the twenty-seven people referred to the trial, one declined consent, four withdrew before therapy commenced and five did not complete the total course of the therapy.

In light of the encouraging results, the next step is to test the therapy’s efficacy in a larger methodologically rigorous clinical trial, in which a comparison is made between AVATAR therapy and a control condition, in order to take account of non-specific elements of therapy exposure, before wider dissemination of the therapy approach.

While the pilot did not include a formal mediation analysis, putative mechanisms emerge from the key treatment ‘phases’. Within the first phase the participants’ key task is to develop assertiveness with the avatar’s character gradually changing to become conciliatory or even helpful in line with the increasing strength and confidence of the person. Commonalities with Cognitive Therapy for Command Hallucinations [16, 15] and other relational approaches [17] along with the pilot findings, suggest that changes in beliefs about voices (specifically related to omnipotence and malevolence) and appraisal of the voice relationship (specifically relative power and assertiveness) are likely mechanisms of action. The second phase specifically targets improvements in self-concept and development of a more positive identity, work that is consistent with recent approaches emphasising the importance of self-esteem and self-compassion in working with distressing voices [21, 22]. Finally, given that anxiety processes are seen as central in the maintenance of distressing voices [9] and that AVATAR therapy involves an exposure to a distressing stimulus (voice content and image), reductions in anxiety may also be an important mechanism of action. With regards to potential moderators, engagement with, and therapeutic response to, cognitive behaviour therapy for psychosis have been predicted by baseline beliefs about illness [23] and social factors such as presence of a caregiver [24]. Given the novelty of the set-up AVATAR therapy may also have more specific treatment moderators. The task of creating a single avatar to represent the person’s voice experience, incorporating discernible verbatim content, suggests that the number of voices, type of content and ratings of the created voice/image may act as additional moderators.

